### Measures

#### Self-report measures

##### Demographics

All participants complete a survey of individual characteristics and demographics, including training program (residency, NP), gender, age, previous suicide prevention training, previous experience with SP procedures, and prior experience (professionally and personally) with suicide. These data will be examined to determine any differences between those who consent for study participation and those who do not, and be used for analytic purposes.

##### Knowledge of suicide and suicide prevention

Participants complete a 17-item multiple choice knowledge assessment before and after viewing online teaching videos and again at 6-month follow-up. The measure assesses knowledge of suicide risk assessment and management as covered in the online teaching program (e.g., “Which of the following best describes risk for suicide?”). A measure of knowledge has been used in published assessments of the CTL training curriculum [27] with good internal consistency (Cronbach’s α = .81–.87) and sensitivity to change (Cohen’s d = .90–1.35). For the purposes of the current study modifications will be made to the measure.

##### Suicide prevention self-efficacy

Participants complete a 20-item measure of self-efficacy at pre- and post-online teaching and again at 6-month follow-up. The measure uses an 8-point Likert scale (ranging from “strongly disagree” to “strongly agree”) to assess trainees’ self-efficacy regarding suicide risk assessment, treatment, and documentation (e.g., “I feel confident that I can ask directly about suicide,” “I feel confident in my knowledge about the key elements of a safety plan.”) The original CTL self-efficacy measure [27] has acceptable internal consistency (Cronbach’s α = .95–.96) and sufficient sensitivity to change over time (Cohen’s d = 1.05–1.15); modifications will be made for the current study.

##### Transfer of training

We also assess participants’ perception that they will transfer what they learned in the online program into clinical practice using an 8-item measure modified from three subscales (transfer design, perceived content validity, opportunity to use) of the Learning Transfer System Inventory [28]. The LTSI subscales have been shown to differentiate trainees who will ultimately use newly trained skills in practice [29]. At post-online teaching and at the 6-month follow up, participants rate items (e.g., “I will be able to use this training on my job,” “It is clear to me that the developers of the training understand how I will use what I learn”) on a 5-point Likert scale (from “strongly disagree” to “strongly agree”). The total of the 8 items will be used as a composite transfer of training score. In addition to being a valid instrument, the LTSI has good internal reliability (Cronbach’s α = 85) [27, 29].

##### Use of suicide prevention skills in practice

At the 6-month follow up, participants complete a 4-item measure rated on a 5-point Likert scale (“not at all” to “frequently”) to assess how often they used the suicide prevention skills taught in the training (e.g., “Since the CTL- PC videos/online teaching program, I have used the suicide prevention skills.”).

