Hypotheses are as follows: 1) All participants will gain suicide prevention knowledge from baseline after viewing online teaching and will maintain improvement at 6-month follow-up; 2) Participants in the experimental group will report greater satisfaction with the training, greater self-efficacy in identifying and responding to patients with suicidal thoughts and plans, and greater intention to use, as well as reported use of suicide prevention skills at 6-month follow-up; and 3) Participants in the experimental group will also be more skillful in responding to suicidal patients (demonstrated during the SP “test case” interview as measured by objective, observed ratings) compared to the control group at 6-month follow-up. Additionally, we will examine moderators of outcomes, differences between the two SP simulation modalities (i.e., face-to- face vs. telehealth modalities), and if there is improvement in skills observed over multiple SP interactions for the experimental group.

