### Procedures

Following enrollment, participants receive an email with instruction to complete online baseline assessments and view the teaching videos within 14 days. All surveys are completed online using the same secure website that hosts the CTL-PC videos. After they have viewed the videos, participants in the experimental condition engage in two practice SP interactions over a period of about four months, with at least one month between interactions. Participants in the control condition do not have practice interactions. At approximately six months following completion of online teaching, both experimental and control participants complete the same face-to-face SP test case. There are two SP character scenarios for the experimental practice sessions and one test case SP scenario.

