All interactions are recorded, securely stored and subsequently coded for observed suicide prevention skills. A portion (at least 20%) of recorded interactions are double coded for inter-rater reliability. Consensus meetings are conducted and discrepancies are resolved through discussion. Additionally, the videos are coded for SPs fidelity to the scenario and feedback procedures. To avoid drift in standardized procedures, SPs receive written feedback on fidelity to the character and feedback delivery.

After the SP test case at approximately 6-month follow-up, all participants complete a final survey including: knowledge and self-efficacy measures, retrospective self-report of transfer of training, intentions to use the suicide prevention training in future practice, self-reported use of suicide prevention skills since the online teaching program, and satisfaction with various aspects of the training.

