Participants in the experiment condition (simulation and feedback) will report greater self-efficacy in identifying and responding to patients at risk for suicide and greater intention to use the skills at 6 months compared to the control condition (those who only complete online teaching). We will use ANCOVA to assess SP training effects on satisfaction with the program, self-efficacy in identifying and managing patients who are at risk for suicide, and greater intention to use the skills at follow up. In all instances, the stratification variables of gender and training program group, as well as race/ethnicity/age and baseline status of the dependent variable (i.e., self-efficacy), will be included as covariates to aid in statistical power [35, 36]. If ceiling effects become an issue in any of these outcomes, tobit regression [37] will be used with the same covariates to assess for condition differences.

##### Exploratory analyses for Hypothesis 2

Moderation effects will be explored. The same ANCOVAs/tobit regressions described above will be conducted for each analysis but will also include interaction effects. Specifically, the cross-product of experimental condition by training group, baseline previous experience with suicidal patients, previous suicide prevention training, and baseline knowledge will be separately entered into each of the analyses. Procedures outlined by Aiken & West [38] will be used to minimize problems associated with multicollinearity. Multiplicative terms will be computed, first by centering each predictor variable and then forming the product term using the centered predictors of interest. Effect sizes, following Lipsey & Wilson [39], will also be examined as power to detect significant interactions will be limited [40]. The goals of these exploratory moderator questions are to better understand for whom the simulation training might be more effective (e.g., Do simulation training effects differ based on previous trainings/experiences with suicidal patients? Do simulation effects differ by training program group?).

##### Hypothesis 3

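### The quoted item on use of skills in practice does not exclude standardized patient sessions, which differ by arm, and reported use is missing from the Hypothesis 2 analysis

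*Protocol article*

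**What the plan says.** All references are to the protocol article.

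- **Hypothesis.** In the Background, Hypothesis 2 predicts that the experimental group will do better on satisfaction, self-efficacy and intention to use the skills, "as well as reported use of suicide prevention skills at 6-month follow-up".
- **Measure.** Under Measures, the section headed "Use of suicide prevention skills in practice" states that "participants complete a 4-item measure rated on a 5-point Likert scale", running from not at all to frequently. One example item is printed: "Since the CTL- PC videos/online teaching program, I have used the suicide prevention skills".
- **Recall window and timing.** Procedures describes the same quantity as "self-reported use of suicide prevention skills since the online teaching program" and fixes when it is collected: "After the SP test case at approximately 6-month follow-up, all participants complete a final survey".
- **Exposure by arm.** Procedures gives experimental participants two practice SP sessions after the videos. For the other arm, "Participants in the control condition do not have practice interactions". Both arms take the SP test case.
- **Analysis.** In the Hypothesis 2 part of Statistical analysis, the hypothesis is restated with self-efficacy and intention only. The method sentence begins "We will use ANCOVA to assess SP training effects on satisfaction with the program, self-efficacy in identifying and managing patients" and ends with intention to use. Reported use appears in neither place.

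**The concern.** A measure of skill use after training is of interest because it speaks to what trainees do with patients. The item as printed asks about any use since the videos. During that time the experimental arm is assigned extra occasions on which the same skills are called for. A trainee in that arm who met no suicidal patient could truthfully report more use than a control trainee who also met none.

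Such a difference would be produced by the assigned intervention itself. Randomisation does not balance it and covariate adjustment does not remove it. A positive result on this outcome could then not be read as evidence that simulation increases use with patients. This is the only listed measure of use after training: the transfer-of-training scale records perception, and the observational coding covers SP encounters.

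The second part concerns the analysis. The article sets out Hypothesis 2 in two places and the outcome lists differ. As the article stands, a hypothesised and measured outcome has no stated comparison. It is also unclear whether it belongs to the set of tests adjusted by the Benjamini-Hochberg method.

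**Working it through.** The article states no power, mean, SD or expected difference for this outcome, so there is no figure to reproduce. The check sets the sections side by side.

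**1. SP sessions inside the recall window**

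The window opens at the online teaching (example item; Procedures) and closes at the final survey, which follows the test case (Procedures).

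| | Practice SP sessions | Test case | Total |
|---|---|---|---|
| Experimental | 2 | 1 | 2 + 1 = 3 |
| Control | 0 | 1 | 0 + 1 = 1 |

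The difference is 3 − 1 = 2 sessions, fixed by the design.

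**2. Do those sessions involve the skills the item asks about?** Yes. Procedures says that participants in an SP session are told to assess suicide risk and to intervene appropriately, which is what the videos teach.

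**3. Does the printed item exclude them?** No. It names no setting and no type of patient. The section heading points to practice, but the article does not show that respondents see that heading or any instruction. Three of the four items (4 − 1 = 3) are not printed. The document therefore neither counts nor excludes SP sessions.

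**4. Could a baseline score help?** No. The measure is taken only at the 6-month follow-up, and its window begins after the videos.

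**5. Hypothesis 2 in its two places**

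| Outcome | Background | Restated hypothesis (Statistical analysis) | ANCOVA list (Statistical analysis) |
|---|---|---|---|
| Satisfaction | yes | no | yes |
| Self-efficacy | yes | yes | yes |
| Intention to use | yes | yes | yes |
| Reported use | yes | no | no |

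Reported use is the only one of the four that drops out of the analysis section altogether. No other section assigns it a test. Data processing gives general rules on alpha, covariates and effect sizes for the hypotheses, but names no outcome-specific comparison for it.

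**The case against.** The strongest reply is that trainees may well not count the SP sessions. The measure is headed as use in practice. The Participants section says that trainees are fully informed that SP interactions are part of their training, and Procedures calls the sessions practice. Someone asked how often they used what the training taught could reasonably leave the training itself out. The article condenses a fuller protocol, and the unshown items or the survey instructions may already restrict use to patients. All of this stands. It limits the point to what the printed item fails to exclude.

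A reader might go further and infer that SP sessions do count as use, so that the experimental arm is bound to score higher, with a large chance of a false positive. The documents do not support that. Any such figure needs an SD and a shift, and neither is given. With 108 participants allocated 1:1 (54 per arm), a two-sided 5% test and a noncentral t with 106 degrees of freedom and noncentrality (shift in SD) × √27, an *assumed* shift of 0.1 SD gives significance about 8% of the time and 0.5 SD about 73%. The answer is simply the assumption restated.

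The share of the scale affected matters as much. Suppose half the experimental arm moves up one category, a shift of 0.50 point, and take an assumed SD of 0.8 to 1.2. Applied to the whole scale, this gives 57% to 90%. If only the printed item is affected, the four-item mean moves by 0.50 / 4 = 0.125 point, and the same SDs give about 8% to 13%. None of these is an estimate for this trial.

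Two further replies have some force. Changing wording in mid-trial creates two versions of the outcome in a small sample. And since the statistical analysis plan is not shown, the missing test can be asserted only of this article. The mismatch between its two statements of Hypothesis 2 remains either way.

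**Conclusion.** The point holds in a limited form. As printed, the item allows SP sessions to be counted, and the arms differ by two such sessions within the recall window. A between-arm difference in reported use could therefore arise without any difference in use with patients. Whether it would, and by how much, is unknown, and no magnitude is claimed. The conclusion rests on the single printed item being representative and on there being no exclusion in the unshown items or instructions.

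The omission of reported use from the Hypothesis 2 restatement and ANCOVA list is a plain textual mismatch and needs no assumption.

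Both parts are minor. They concern a secondary self-report outcome. The primary comparison, observed skills at the test case under Hypothesis 3, does not use this measure and is unaffected.

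**What to change.** 1. **Check the full survey.** If the other items or the instructions already limit use to real patients, say so in the protocol; no change to the survey is then needed.
2. **Otherwise reword for remaining participants.** Make the use items refer to use *with real patients, not counting the standardized patient sessions*. Flag responses given under the present wording with a version indicator, or label them as possibly including SP sessions.
3. **Reconcile the two statements of Hypothesis 2.** Either add reported use to the restated hypothesis, to the ANCOVA (or tobit) list and to the Benjamini-Hochberg set, noting that it has no baseline score to adjust for, or remove it from the Background.
4. **Optional.** Ask how many patients with suicidal thoughts the trainee saw in the period, so that use can be read against opportunity.

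The cost is a wording change in an online survey to which the team has already added an item during the study (Discussion, on concurrent training), plus a one-line edit to the analysis section. The drawback is that those already surveyed answered the present wording, so the outcome will exist in two versions among the planned 108 participants.

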##### Satisfaction with suicide prevention training

At 6-month follow up, participants complete a 12-item measure of satisfaction with the training using a 5-point Likert scale (“not at all satisfied” to “very satisfied”). Participants are asked about their satisfaction with aspects of the training videos, (e.g., quality, duration, accessibility, and amount of information), as well as with their SP experience(s) (e.g., realism, quality of feedback).

#### Observational ratings

##### Observational coding

Video recordings of SP practice interactions and SP test case interactions for all participants are coded by a research team using an objective observational coding measure with five domains of skills related to the training: non-anxious and empathic presence, assessment of risk factors, assessment of protective factors, asking about suicidal ideation and behavior, and safety planning. Initial development work established acceptable inter-rater reliability using Gwet’s AC1 statistic, which is considered preferable to Cohen’s Kappa in cases when raters produce ratings that are not necessarily statistically independent [30]. Participants are also rated (“needs work,” “acceptable work,” and “good work”) on a general quality item (e.g., degree of collaboration, tone).

##### Feedback matrix

Immediately following each interaction, SPs prepare feedback for the participant on 15 items and document the ratings on a Scantron-style form. SPs verbally provide participants with six feedback items – three positive and three constructive. Several items are prioritized as feedback items to provide to the participant. In the case of experimental participants’ second and final sessions, SPs have information on the feedback items that have been previously provided to the participant as guidance for novel feedback.

##### Standardized patient fidelity

Coders assess SP fidelity to the character scenario and procedures using a 9-item actor fidelity measure coded as “present,” “absent,” or “not-applicable.” For example, the SP is rated on affect (displays affect consistent with character) and sequence and timing of disclosure (“sometimes I wonder if I should end it all” within 7 min if not already asked directly).

#### Materials

##### Equipment

In-person sessions are recorded with a webcam and microphone using computer software called Debut Video Capture. Telehealth sessions are also recorded with the same equipment using a secure video conferencing and recording software (Zoom). Recordings are uploaded to a secure website for storage and access for coding.

##### Standardized patient scenarios

Three scenarios were developed for the study with input from subject matter experts. Each scenario features an older adolescent/young adult primary care patient experiencing suicidal thoughts in the context of stressful life events. The three scenarios were matched for upstream factors (e.g., life stressors, social support) and difficulty. A male and a female scenario are modified slightly for telehealth interactions (experimental condition). The scenario used for the SP test case that all participants receive is an in-person female scenario. Choice of female gender for the test case reflects the greater proportion of suicide attempts in females.

### Statistical analysis

#### Data processing

Data collection and storage is managed by REDCap, a secure software system supported by the institution. (Data management procedures are fully described in the study manual.) A baseline check of randomness will be conducted for each demographic and outcome variable collected. Because we are interested in establishing equivalence (as opposed to detecting differences), a more conservative alpha level will be applied (α = .20). Categorical variables will be analyzed using chi-square tests; continuous variable differences will be assessed using a general linear model approach (ANOVA). Any baseline difference will be controlled for statistically in all subsequent analyses. For analyses related to hypotheses, α = .05 and covariates will include stratification variables of gender and residency/NP training program, race/ethnicity, age, and the specific outcome baseline score as well as any other variables found to differ at baseline. Effect sizes (Hedge’s *g*) will also be examined for each of the study hypotheses.

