### Design

The study is a randomized controlled trial with an experimental group and a control group allocated with a 1:1 randomization ratio. All trainees are randomized to control and experimental learning groups using Wei’s urn randomization [23] which provides overall balance at the end of accrual but also gives good, often near-perfect, balance within many strata [24, 25]. Randomization strata include medical learner groups (i.e., medical residents, pediatric residents, and nurse practitioners) and gender. After all baseline measures are completed, participants are randomized to experimental condition by the project statistician, who remains blinded to study condition.

Participants in both groups complete a 48-min, 6-module, online video-based training on suicide prevention (Commitment to Living for Primary Care; CTL-PC). Upon completion of the online teaching program, participants in the experimental group engage in two standardized patient practice interactions over the course of 4 to 6 months. One practice interaction takes place in-person and the other uses a telehealth model. The order is randomized. Then, approximately 6 to 8 months (depending on schedules, see below) after video-based learning, both control and experimental groups engage in an in-person “test case” standardized patient interaction.

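### Baseline significance tests at α = .20 are treated as evidence of equivalence and decide which covariates join the prespecified core, so the final models are not fixed in advance

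*Protocol article*

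**What the plan says.** The Data processing section of the protocol article sets out a rule in four steps.

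- **Scope.** "A baseline check of randomness will be conducted for each demographic and outcome variable collected".
- **Method.** "Categorical variables will be analyzed using chi-square tests; continuous variable differences will be assessed using a general linear model approach (ANOVA"). No margin is attached to these tests.
- **Justification.** "Because we are interested in establishing equivalence (as opposed to detecting differences), a more conservative alpha level will be applied", namely α = .20.
- **Consequence.** "Any baseline difference will be controlled for statistically in all subsequent analyses".

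The same section fixes a core set for the hypothesis analyses: "covariates will include stratification variables of gender and residency/NP training program, race/ethnicity, age, and the specific outcome baseline score". Variables found to differ at baseline are added to that core.

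Three other sections bear on the rule.

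- **Design** places randomisation after completion of all baseline measures. It also gives the strata: "Randomization strata include medical learner groups (i.e., medical residents, pediatric residents, and nurse practitioners) and gender".
- **Hypothesis 1** says that equivalence needs a minimum important difference (MID) set beforehand, and sets it at a standardised .20.
- **Hypothesis 3**, the primary hypothesis, lists gender, training program group, race/ethnicity and age for the ANCOVA. It names no variable selected by a baseline test.

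**The concern.** There are two faults in the rule and two inconsistencies around it.

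1. **Selection by imbalance, not prognosis.** Under valid randomisation a baseline difference between arms is a chance event. Its p-value says nothing about whether the variable predicts the outcome. A useful predictor that happens to be balanced stays out, and a useless one that happens to be imbalanced goes in. The final model is unknown until the data are seen, and the standard errors take no account of the selection step.
2. **Non-significance read as equivalence.** Raising α makes a difference test more likely to flag something, but it does not turn it into an equivalence test. The plan applies the correct principle under Hypothesis 1 and not here.
3. **The primary model is described in two ways.** Data processing sends flagged variables into all later analyses; the Hypothesis 3 list contains none.
4. **Levels of the learner-group covariate.** Randomisation used three learner groups, whereas Data processing describes the stratification covariate as residency/NP.

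The primary outcome is the most exposed. Skills are first observed in the standardised patient sessions, after the videos, so no pre-randomisation skill score is available to adjust for. Any precision beyond the four listed covariates must come from other baseline variables, and under this rule those can enter only by failing a balance test.

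**Working it through.** **Inputs.** α = .20 per baseline test (Data processing). N = 108 (Power analyses) with 1:1 allocation (Design), so 54 per arm. MID = .20 SD (Hypothesis 1). Candidates outside the core, from Demographics: prior suicide-prevention training, prior standardised patient experience, and professional and personal experience with suicide, which makes 4. Baseline knowledge and self-efficacy make 6 for the skills outcome.

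**Check of the set-up.** The plan gives no figure for the baseline rule itself. Its first power figure confirms the reading of N. With d = .30 and R² = .40, the noncentrality is .30 × √(108/4) / √(1 − .40) = .30 × 5.196 / .775 = 2.01. Two-sided power at .05 is then .514, matching the stated .51. The section's other power figures are not used here.

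**Chance entries.** If the tests are independent, the expected number is .20k and P(at least one) = 1 − .80^k.

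- k = 4: expected 0.8; 1 − .410 = .59.
- k = 6: expected 1.2; 1 − .262 = .74; 2⁶ = 64 possible models.

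**What passes as no difference.** The largest observed standardised difference that is not significant at two-sided .20 is t(.90; 106 df) × √(4/108) = 1.2896 × 0.19245 = 0.248 SD, which exceeds the MID of .20. The same 0.248 is the half-width of the 80% interval for the difference. Even two identical observed means would therefore leave differences beyond .20 SD inside that interval, and no continuous baseline variable could meet the Hypothesis 1 criterion at this sample size.

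**Effect on inference.** ANCOVA was simulated with 54 per arm, independent normal covariates, simple 1:1 allocation and d = .30, comparing covariates added at p < .20 with the same covariates always included. The plan does not say how prognostic the candidates are, so a range is shown. In the first three rows R² is the share of variance left after the core, and d is in those residual SDs. The last three rows have no separate core.

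| Candidates | R² (assumed) | Power, selected | Power, fixed | Type I error, selected |
|---|---|---|---|---|
| 6 | .05 | .33 | .34 | about .04–.05 |
| 6 | .10 | .34 | .36 | about .04–.05 |
| 6 | .20 | .33 | .38 | about .04–.05 |
| 3 | .20 | .35 | .41 | .040 |
| 5 | .30 | .34 | .43 | .035 |
| 5 | .50 | .36 | .58 | .026 |

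In the last three rows the fixed set had type I error of .048 to .052. With 4,000 runs the Monte Carlo standard error of a power near .35 is √(.35 × .65 / 4000) = .008, so the gaps in the first two rows are barely distinguishable from noise. The test becomes conservative because an unflagged predictor leaves its variance in the residual while its imbalance is, by construction, small. The standard error then overstates the true uncertainty.

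**The case against.** The strongest reply is that the rule only tops up a sensible prespecified core, that it catches the larger observed imbalances, and that it does little harm. Much of this stands.

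- **A reader might infer that the tests choose all covariates, or that chance decides the primary model.** The text does not support this. Gender, training program, race/ethnicity, age and, where one exists, the outcome's baseline score are fixed. The Hypothesis 2 and Hypothesis 3 sections repeat fixed lists. Chance decides only the additions.
- **A reader might infer a raised false-positive risk.** The simulations show the opposite.
- **A reader might say that the tests miss true imbalances.** With baseline measured before randomisation there is no true difference between arms to miss. What matters is the observed difference, and above 0.248 SD it is flagged.
- **The 59% to 74% range depends on independence.** Prior training, experience, knowledge and self-efficacy are probably correlated, which would lower it. When knowledge or self-efficacy is the outcome, its own baseline is already in the core.
- **The large power loss needs strongly prognostic candidates.** The document shows no evidence that any of them predicts observed skill that well. The Power analyses section expects baseline values and other baseline variables together to explain about half of the variance, but does not say which.
- **A reader might infer that the three strata are certainly collapsed to two.** Data processing reads that way ("covariates will include stratification variables of gender and residency/NP training program"), but the Hypothesis 2 and 3 sections say training program group without giving levels, and that could mean three. At most the split among residents is lost.

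The reply does not rescue the equivalence claim, which the plan's own Hypothesis 1 section contradicts. It also does not settle which covariates enter the primary ANCOVA.

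**Conclusion.** The point holds, at moderate weight. The baseline tests cannot establish equivalence: observed differences up to 0.248 SD pass, against the plan's own margin of .20 SD, assuming 54 per arm. The rule for adding covariates leaves the final models open, with a 59% to 74% chance of at least one chance addition under independence and four to six candidates. Its cost is a conservative test and lost power: one or two percentage points if the candidates explain 5% to 10% of the variance left after the core, about five at 20%, and more at the higher assumed R². It is not an inflated error rate, and it does not affect the prespecified core. The Data processing and Hypothesis 3 sections need reconciling in any case. The learner-group levels are a minor clarification.

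**What to change.** 1. In Data processing, delete the baseline significance tests, the equivalence statement and the conditional-adjustment rule, including its repetition at the end of the covariate list. Report baseline characteristics by arm descriptively.
2. Keep the prespecified core, including age and race/ethnicity. Before outcome data are seen, add a short list justified by expected prognosis, drawn from baseline knowledge, baseline self-efficacy, prior suicide-prevention training and prior standardised patient experience.
3. Use the same list in Data processing and Hypothesis 3, and say that the outcome's baseline score applies only where one is collected before randomisation.
4. Code learner group with the three levels used in randomisation.
5. Label any other adjustment as a sensitivity analysis.

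The cost is analysis wording and a few model degrees of freedom out of 108 participants: one for the third learner-group level and about one for each added covariate. No change to data collection is needed.
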